**Analysis plan**

Data collection: categorical data will be presented as absolute numbers and percentages. Continuous data will be presented as mean ± standard deviation. Participants will be classified into several groups based on CAVI value. Baseline characteristics was compared among them. The effect of CAVI on each endpoint will be analyzed using the proportional hazard model. Incremental prognostic value was analyzed with likelihood ratio test, ROC (receiver operating characteristic) curve analysis, NRI (net reclassification improvement), and IDI (integrated discrimination improvement). The cutoff for CAVI against the incidence of cardiovascular events will be determined by ROC analysis.

**Appendix:** **Definition of adverse events**

| **Primary Endpoint** | 1. Cardiovascular death  2. Nonfatal myocardial infarction  3. Nonfatal stroke |
| --- | --- |
| **Secondary Endpoint** | 1. All cause death  2. Angina pectoris with revascularization  3. New incidence of peripheral arterial disease (arteriosclerosis obliterans)  4. Aortic aneurysm  5. Aortic dissection  6. Heart failure with hospitalization  7. Deterioration in renal function (dialysis or renal transplantation) |

**Cardiovascular death**

The cause of death will be determined by the principal condition that caused the death, not the immediate mode of death. CEC members will review all available information and use their clinical expertise to adjudicate the cause of death. All deaths not attributed to the categories of cardiovascular (CV) death and not attributed to a non-CV cause are presumed CV deaths and are part of the CV mortality outcome. Death certificates or summaries, if possible, including the date of death and other relevant details, will be provided for all patients who have died. However, if a death certificate is the only information available for review in addition to the patient data in the clinical trial database, the CEC may decide not to use this information as cause of death if another etiology appears more plausible. The following definitions will be used for the adjudication of fatal cases:

Sudden cardiac death. Death that occurs unexpectedly in a previously stable patient and includes the following:

• Witnessed and instantaneous death without new or worsening symptoms

• Witnessed death within 60 minutes of the onset of new or worsening cardiac symptoms

• Witnessed death attributed to an identified arrhythmia (e.g., captured by electrocardiogram or witnessed on a monitor by either a medic or paramedic)

• Subject unsuccessfully resuscitated from cardiac arrest or successfully resuscitated from cardiac arrest that dies within 24 hours without identification of a non-cardiac etiology

• Un-witnessed death with no conclusive evidence of another, non-CV, cause of death (i.e. presumed CV death).

Sudden death attributable to acute myocardial infarction (MI) (MI type 3). Sudden death occurring up to 14 days after a documented acute MI (verified either by the diagnostic criteria outlined for acute MI or by autopsy findings showing recent MI or recent coronary thrombus) where there is no conclusive evidence of another cause of death. If death occurs before the biochemical confirmation of myocardial necrosis can be obtained, adjudication should be based on clinical presentation and ECG evidence.

Death attributable to heart failure or cardiogenic shock. Death occurring in the context of clinically worsening symptoms and/or signs of congestive heart failure (CHF) without evidence of another cause of death.

New or worsening signs and/or symptoms of CHF include any of the following:

• New or increasing symptoms and/or signs of heart failure requiring the initiation of, or an increase in, treatment directed at heart failure or occurring in a patient already receiving maximal therapy for heart failure

• Heart failure symptoms or signs requiring continuous intravenous therapy or oxygen administration

• Confinement to bed predominantly because of heart failure symptoms

• Pulmonary edema sufficient to cause tachypnea and distress not occurring in the context of an acute MI or as the consequence of an arrhythmia occurring in the absence of worsening heart failure

• Cardiogenic shock not occurring in the context of an acute MI or as the consequence of an arrhythmia occurring in the absence of worsening heart failure

– Cardiogenic shock is defined as systolic blood pressure (SBP) <90 mmHg for more than 1 hour, ack of response to fluid resuscitation and/or heart rate correction, and judged to be secondary to cardiac dysfunction and associated with at least one of the following signs of hypoperfusion:

1. Cool, clammy skin
2. Oliguria (urine output <30 mL/hour)
3. Altered sensorium
4. Cardiac index <2.2 L/min/m^2^

Cardiogenic shock can also be defined in the presence of SBP ≥90 mmHg or for a time period <1 hour if the blood pressure measurement or time period is influenced by the presence of positive inotropic or vasopressor agents alone and/or with mechanical support <1 hour. The outcome of cardiogenic shock will be based on CEC assessment and must occur after randomization. Episodes of cardiogenic shock occurring before and continuing after randomization will not be part of the study outcome. This category will include sudden death occurring during an admission for worsening heart failure

Death attributable to stroke or cerebrovascular event. Death occurring up to 30 days after a stroke that is either attributable to the stroke or caused by a complication of the stroke.

Death attributable to other CV causes. Death must be caused by a fully documented CV event not included in the above categories (e.g. dysrhythmia, pulmonary embolism, or CV intervention). Death attributable to an MI that occurs as a direct consequence of a CV investigation/procedure/operation will be classified as death due to another CV cause.

Non-CV death

Non-CV death is defined as any death not covered by cardiac death or vascular death. The CEC will be asked to determine the most likely cause of non-CV death. Examples of non-CV death are pulmonary causes, renal causes, gastrointestinal causes, infection (including sepsis), non-infectious causes (e.g., systemic inflammatory response syndrome), malignancy (i.e., new malignancy, worsening of prior malignancy), hemorrhage (not intracranial), accidental/trauma, suicide, non-CV organ failure (e.g., hepatic failure) or non-CV surgery.

**Myocardial infarction (non-fatal)**

The term MI should be used when there is evidence of myocardial necrosis in a clinical setting consistent with myocardial ischemia. Under these conditions, any one of the following criteria (A and B) meets the diagnosis for myocardial infarction.

A. Spontaneous MI (type 1)

To identify a type 1 MI, patients should demonstrate spontaneous symptoms of myocardial ischemia unprovoked by supply/demand inequity, together with ≥1 of the following criteria:

• Cardiac biomarker elevation: Troponin is the preferred marker for adjudicating the presence of acute MI. At least one value should show a rise and/or fall from the lowest cut-point providing 10% imprecision (typically the upper reference limit for the troponin run per standard of clinical care). Creatine kinase-MB is a secondary choice of marker to troponin; a rise in CK-MB above the local upper reference limit would be consistent with myocardial injury.

• ECG changes consistent with new ischemic changes

– ECG changes indicative of new ischemia (new ST-T changes or new left bundle branch block [LBBB]) or ECG manifestations of acute myocardial ischemia (in the absence of left ventricular hypertrophy [LVH] and LBBB):

– Development of pathological Q waves in the ECG

1. Any Q-wave in leads V2–V3 ≥0.02 seconds or QS complex in leads V2 and V3
2. Q-wave ≥0.03 seconds and ≥0.1 mV deep or QS complex in leads I, II, aVL, aVF, or V4-V6 in any two leads of a contiguous lead grouping (I, aVL, V6; V4-V6; II, III, and aVF)

– ST elevation: New ST elevation at the J-point in two contiguous leads with the cut-off points: ≥0.2 mV in men or ≥0.15 mV in women in leads V2–V3 and/or ≥0.1 mV in other leads

– ST depression and T-wave changes: New horizontal or down-sloping ST depression ≥0.05 mV in two contiguous leads and/or T inversion ≥0.1 mV in two contiguous leads with prominent R-wave or R/S ratio >1

• Imaging evidence of new non-viable myocardium or new wall motion abnormality

B. “Demand”-related (type 2) MI

Patients with type 2 MI should be considered under similar diagnostic criteria as a type 1 MI; however, type 2 MI should be considered present when myocardial ischemia and infarction are consequent to supply/demand inequity, rather than a spontaneous plaque rupture and coronary thrombosis.

C. Percutaneous coronary intervention (PCI)-related MI (type 4a/4b)

For PCI in patients with normal baseline troponin values, elevations of cardiac biomarkers above the 99th percentile URL within 24 hours of the procedure are indicative of peri-procedural myocardial necrosis. By convention, increases of biomarkers >3 × 99th percentile URL (troponin or CK-MB >3 × 99th percentile URL) are consistent with PCI-related MI.

Where the cardiac biomarker is elevated prior to PCI, a ≥20% increase in the value of the second cardiac biomarker sample within 24 hours of PCI and documentation that cardiac biomarker values were decreasing (two samples ≥6 hours apart) prior to the suspected recurrent MI are consistent with PCI-related MI.

Symptoms of cardiac ischemia are not required.

D. Coronary artery bypass grafting (CABG)-related MI (type 5)

For CABG in patients with normal baseline troponin values, elevation of cardiac biomarkers above the 99th percentile URL within 72 hours of the procedure is indicative of peri-procedural myocardial necrosis. By convention, an increase of biomarkers >5 × 99th percentile URL (troponin or CK-MB >5 × 99th percentile URL) plus at least one of the following is consistent with CABG-related MI:

• New pathological Q waves in at least two contiguous leads on the ECG that persist for 30 days, or new LBBB

• Angiographically documented new graft or native coronary artery occlusion

• Imaging evidence of new loss of viable myocardium

If the cardiac biomarker is elevated prior to CABG, a ≥20% increase in the value of the second cardiac biomarker sample within 72 hours of CABG and documentation that cardiac biomarker values were decreasing (two samples ≥6 hours apart) prior to the suspected recurrent MI plus new pathological Q-waves in ≥2 contiguous leads on the electrocardiogram; or new LBBB, angiographically documented new graft, or native coronary artery occlusion; or imaging evidence of new loss of viable myocardium are consistent with a periprocedural MI after CABG. Symptoms of cardiac ischemia are not required.

Clinical classification of acute MI. Every MI identified by the CEC will be classified into one of the following categories:

• Type 1: Spontaneous MI related to ischemia arising from a primary coronary event such as plaque erosion and/or rupture, fissuring, or dissection

• Type 2: MI secondary to ischemia attributable to either increased oxygen demand or decreased supply, e.g. coronary artery spasm, coronary embolism, anemia, arrhythmias, hypertension, or hypotension

• Type 3: Sudden unexpected cardiac death, including cardiac arrest, often with symptoms suggestive of myocardial ischemia, accompanied by presumably new ST elevation, new LBBB, or evidence of fresh thrombus in a coronary artery by angiography and/or at autopsy, with death occurring before blood samples could be obtained or before the appearance of cardiac biomarkers in the blood

• Type 4a: MI associated with PCI

• Type 4b: MI associated with stent thrombosis as documented by angiography or at autopsy

• Type 5: MI associated with CABG

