**Angina pectoris with coronary revascularization**

• Angina pectoris includes stable and unstable angina pectoris.

For diagnosis of unstable angina, the subject must first have had an episode of ischemic discomfort consistent with unstable angina (ischemic discomfort either at rest, of new onset, or in an accelerating pattern) lasting ≥10 minutes, which occurred before the subject presented to the hospital. However, if an increase of biomarkers >5 × 99th percentile URL (troponin or CK-MB >5 × 99th percentile URL) is observed, diagnosis will be myocardial infarction.

• Coronary Revascularization

Attempted revascularization procedures, even if not successful, will be counted. Revascularization is divided by type and urgency. Planned revascularization is defined as ischemia-driven coronary revascularization (PCI or CABG). The evaluation of invasive or non-invasive functional ischemia is essential before PCI. Urgent revascularization is defined as coronary revascularization (PCI or CABG) that occurred during a hospitalization prompted by unstable angina with an episode of ischemic discomfort at rest lasting at least 10 minutes.

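### The MI definition requires necrosis, but its type 1 list can be met by ischemia-only findings, so the same biomarker-negative episode can be scored as a primary-endpoint MI or as angina

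*Protocol*

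**What the plan says.** The definition is in the protocol's Appendix, under Myocardial infarction (non-fatal). It opens with a general condition: "The term MI should be used when there is evidence of myocardial necrosis in a clinical setting consistent with myocardial ischemia". A linking sentence follows: "Under these conditions, any one of the following criteria (A and B) meets the diagnosis for myocardial infarction".

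Criterion A (type 1) then reads: "patients should demonstrate spontaneous symptoms of myocardial ischemia unprovoked by supply/demand inequity, together with ≥1 of the following criteria". Three criteria are listed:

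- Biomarker elevation, with the remark "Troponin is the preferred marker for adjudicating the presence of acute MI". Troponin is preferred; neither it nor any other marker is stated to be mandatory.
- "ECG changes consistent with new ischemic changes". This covers new ST-T change, new left bundle branch block (LBBB) and pathological Q waves.
- "Imaging evidence of new non-viable myocardium or new wall motion abnormality".

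Criterion B (type 2) refers back to criteria like those for type 1 and adds that ischemia and infarction arise from a supply/demand imbalance.

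The Appendix section Angina pectoris with coronary revascularization sets another boundary. An unstable angina episode is called MI on "an increase of biomarkers >5 × 99th percentile URL". It states no other trigger.

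**The concern.** The opening sentence is about necrosis, but the list that carries it out mixes two kinds of finding. A biomarker rise, pathological Q waves and new non-viable myocardium can stand as evidence of infarction. New ST-T change, new LBBB and a new wall motion abnormality can reflect ischemia without it. The rule gives all of them equal weight, and one is enough.

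Non-fatal MI is one of three components of the primary endpoint (section 5) and is also examined on its own (section 4, first secondary objective). Angina counts only as a secondary endpoint, and only with revascularization. So the wording decides whether an episode enters the primary endpoint, the secondary endpoint or neither. The eligible population includes patients with a history of coronary disease, angina among it (section 7), so such episodes are foreseeable. Any that are scored as MI feed the proportional hazards model, the ROC, NRI and IDI analyses and the ROC-derived CAVI cutoff (section 14).

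**Working it through.** No arithmetic applies; the check is one of logic. Take three episodes, all with spontaneous ischemic symptoms, and apply each rule in turn.

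| Episode | Type 1 list alone (at least 1 of 3) | Necrosis sentence and list together | Angina section |
| --- | --- | --- | --- |
| 1. New horizontal ST depression of 0.05 mV in two contiguous leads; biomarkers normal; no imaging finding | MI | Not MI, unless necrosis is shown in some other way | Trigger not met: unstable angina |
| 2. New pathological Q waves; biomarkers normal | MI | MI, if Q waves are accepted as evidence of necrosis | Trigger not met |
| 3. Biomarker rise above 5 times the 99th percentile limit | MI | MI | MI |

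Episode 3 is classified alike throughout. Episode 1 has two answers inside the MI section itself, and the angina section sides with the stricter one. Episode 2 shows that the difficulty does not extend to every ECG or imaging item.

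Next, can the linking sentence settle Episode 1? Let N be the evidence that satisfies the necrosis condition, and L the list.

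1. The section does not say what N is for types 1 and 2. The only evidence it names is L.
2. Suppose N means a biomarker rise, Q waves or non-viable myocardium. Each of these is already in L, so a symptomatic patient who has N automatically has at least one item of L. N and L together then reduce to N, and the ST-T, LBBB and wall-motion items can never decide a case.
3. Suppose instead that those items are meant to decide cases. Then L must itself serve as the evidence of necrosis, the opening sentence adds nothing, and Episode 1 is MI.

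Either the opening sentence or a large part of the list has no effect, and the text does not say which.

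The neighboring rules show that a stricter form was available. For bypass surgery with normal baseline troponin, the Appendix requires a biomarker rise above 5 times the limit and, in addition, at least one further finding. The PCI rule also rests on biomarkers. Among criteria A to D, only types 1 and 2 have no stated biomarker requirement.

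**The case against.** The strongest reply is that the linking sentence makes necrosis a precondition: A and B operate only once it is present. On that reading Episode 1 fails, and a blinded committee reading the whole section would not score it as MI. Type 2 names infarction a second time, and the angina section already keeps biomarker-negative episodes on the angina side. The ECG items also carry conditions of lead, ST shape and R wave that remove many trivial changes.

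Much of this stands. A reader might infer that the protocol simply counts chest pain with an ECG change and normal troponin as a primary-endpoint MI. The documents do not support that: it follows only if the list is applied apart from its lead-in. The defensible statement is that such an episode can be counted.

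What does not stand is that the lead-in cures the rule. It gives no operational meaning to necrosis for types 1 and 2, and read strictly it leaves the ischemia-only items with nothing to do. The ECG conditions narrow the set of episodes but do not turn ischemia into infarction. Section 12 has the Clinical Endpoint Review Committee work to prespecified criteria, so two careful adjudicators could classify Episode 1 differently, each with support in the text.

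**Conclusion.** The point holds as an unreconciled definition. The necrosis sentence, the type 1 list (carried over to type 2) and the angina section can give different answers for a symptomatic, ECG-positive, biomarker-negative episode, and one of those answers places it in the primary endpoint. It should be corrected. The gap is confined to the ST-T, LBBB and wall-motion items.

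The direction for counts is clear: reading the list alone can only add MIs relative to the stricter reading. The effect on the CAVI association has no predictable sign, since it depends on how CAVI relates to the added episodes.

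The size cannot be derived. A reader might be tempted to apply the 4.6% five-year risk in section 14 to 3,000 subjects and take a share of the result. That risk is for cerebrovascular events. The protocol gives no MI rate, no MI share of the primary endpoint and no frequency of biomarker-negative episodes, so a percentage inflation would be guesswork. Nor does the point touch the sample size, which rests on cerebrovascular events.

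**What to change.** Reconcile the two Appendix sections:

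- For type 1 and type 2 MI, require evidence of necrosis explicitly: a biomarker rise and/or fall, or new pathological Q waves, or new non-viable myocardium.
- Keep ST-T change, new LBBB and wall motion abnormality as supporting evidence that cannot qualify an event alone.
- Have the blinded committee classify biomarker-negative ischemia without infarct evidence as angina, and word the angina section to match. Its biomarker multiple differs from the lower cut-point in the MI section. That is a separate mismatch, but the same edit should leave one boundary stated in both places.
- For events already adjudicated, either re-read the MIs that lack a biomarker rise, blinded to CAVI, or leave the adjudication as it is and report a sensitivity analysis without them.

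The cost is some wording, some committee time and perhaps slightly fewer primary events. There is also a cost in credibility: the competing-risk figure and table at the end of the protocol file show that outcome analyses have already been run. Any change to a primary component now should be dated, justified and shown to have been made without reference to CAVI. If that cannot be shown, the sensitivity analysis is the safer choice.

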**Stroke (non-fatal)**

The rapid onset of a new persistent neurologic deficit attributed to an obstruction in cerebral blood flow and/or cerebral hemorrhage with no apparent non-vascular cause (e.g., trauma, tumor, or infection). Available neuroimaging studies must be considered to support the clinical impression and to determine if there is a demonstrable lesion compatible with an acute stroke. Strokes will be classified as ischemic, hemorrhagic, or unknown.

Diagnosis of stroke. For the diagnosis of stroke, the following four criteria should be fulfilled:

• Rapid onset of a focal/global neurological deficit with at least one of the following:

– Change in level of consciousness

– Hemiplegia

– Hemiparesis

– Numbness or sensory loss affecting one side of the body

– Dysphasia/aphasia

– Hemianopia (loss of half of the field of vision of one or both eyes)

– Other new neurological sign(s)/symptom(s) consistent with stroke

Note: If the mode of onset is uncertain, a diagnosis of stroke may be made provided that there is no plausible non-stroke cause for the clinical presentation

• Duration of a focal/global neurological deficit ≥24 hours OR <24 hours if attributable to at least one of the following therapeutic interventions:

– Pharmacologic (i.e., thrombolytic drug administration)

– Non-pharmacologic (i.e., neurointerventional procedure such as intracranial angioplasty)

or

– Available brain imaging clearly documents a new hemorrhage or infarct

or

– The neurological deficit results in death

• No other readily identifiable non-stroke cause for the clinical presentation (e.g., brain tumor, trauma, infection, hypoglycemia, peripheral lesion)

• Confirmation of the diagnosis by at least one of the following:*

– Neurology or neurosurgical specialist

– Brain imaging procedure (at least one of the followings):

1. CT scan
2. MRI scan
3. Cerebral vessel angiography

– Lumbar puncture (i.e. spinal fluid analysis diagnostic of intracranial hemorrhage)

If a stroke is reported but evidence of confirmation of the diagnosis by the methods outlined above is absent, the event will be discussed at a full CEC meeting. In such cases, the event may be adjudicated as a stroke on the basis of the clinical presentation alone, but full CEC consensus will be mandatory.

If the acute focal signs represent a worsening of a previous deficit, these signs must have either

• Persisted for more than one week

or

• Persisted for more than 24 hours and accompanied by an appropriate new CT or MRI finding

Classification of stroke. Strokes are sub-classified as follows:

• Ischemic (non-hemorrhagic): A stroke caused by an arterial obstruction attributable to either a thrombotic (e.g., large vessel disease/atherosclerotic or small vessel disease/lacunar) or embolic etiology. This category includes ischemic stroke with hemorrhagic transformation (i.e. no evidence of hemorrhage on an initial imaging study but appearance on a subsequent scan)

• Hemorrhagic: A stroke caused by a hemorrhage in the brain as documented by neuroimaging or autopsy. This category will include strokes attributable to primary intracerebral hemorrhage (intraparenchymal or intraventricular), subdural hematoma and primary subarachnoid hemorrhage

• Not assessable: The stroke type could not be determined by imaging or other means (e.g., lumbar puncture, neurosurgery, or autopsy) or no imaging was performed.

